### Budget impact analysis

The annual budget impact analysis (BIA) will be performed from the perspective of the clinics [40, 41]. The aim of the BIA is to assess the additional cost each clinic will incur to implement and sustain the EBI. The population of interest for the BIA will be the patients served by each clinic who are eligible to receive a mammogram for each year under study. Each patient will be the unit of analysis for the purpose of estimating the volume and resources required. The dollar value and the price rates for the expenditures incurred by each clinic will be standardized at the final year of the study for the BIA. This standardization will circumvent the need to use discount factors and inflation adjustment for the annual BIA values pertaining to each year of the study. The average cost per year will be computed for three different time periods:The pre-intervention/control period, which will give us a distribution of cost for the screening reminder or navigation systems currently used by the clinics. We expect to find a wide variety of patient navigation or screening reminder systems during this period. Many clinics might have no mechanism in place for navigation or screening reminders for mammogram eligible patients.The intervention period, which will help estimate the initial investment and implementation cost associated with the EBI. Cost associated with this period will be the highest among the three periods and will provide an estimate of the upfront expenses for any new clinic establishing an EBI program. It will consists of the fixed cost of training the navigators on the EBI methods, cost associated with structural changes to the clinic’s EMR, which will help link the patient records with the appropriate EBI scripts, and cost of developing web-based scripts for patient navigation. Based on the volume of patients served, the intervention period cost will also include the variable cost of hiring additional navigators for implementing the EBI. The navigators will not only help improve the provision of mammograms but also facilitate diagnostic test administration and treatment initiation for patients who need these. The patient volume and amount of time required per patient will be obtained during the implementation period from each of the clinics. The initial time required to navigate a patient and improve adherence to the mammogram screen will be similar between patients. However, if the patient has a positive mammogram, the patient will require further navigation to obtain a diagnostic test (biopsy). Patients with positive diagnostic tests will also require navigation for treatment initiation. Although the study’s primary goal is to improve screening adherence and reduce screening “no-show” rates, the navigators are also involved with diagnostic and treatment navigation when required by the patient. Hence, cost of those tasks will also be included in the analysis.The post-intervention period, which will help estimate the steady state cost for each clinic with no external support for the EBI. Post-intervention provision of EBI and associated costs will be obtained 3 months after the end of the study.

### Trial status

The trial has completed enrollment of the first wave of clinics (*n* = 9) and is currently collecting baseline measures at these locations. Baseline measures include appointment adherence outcomes as described above, the clinic and patient resource utilization survey for the budget impact analysis, and CFIR survey. All participating clinics have completed the baseline CFIR survey. Based on the number of mammography screening drives at each clinic, we anticipate enrolling approximately 2200 women into the first wave of the trial.

## Discussion

### Rationale for the stepped wedge design

While parallel group randomized controlled trials (RCT) are considered the gold standard for evaluating EBI efficacy, withholding an effective EBI in practice can be seen as unethical and/or impractical [42–45] . The stepped wedge design addresses this issue by enabling all clinics to eventually receive the EBI during the study and allowing each clinic to serve as its own control, while maintaining strong internal validity [42–45]. Stepped wedge designs are particularly useful when the intervention is thought to do more good than harm and when an RCT is impractical, as is the case in this study (e.g., financial, logistical reasons) [45–47].

### Anticipated challenges

Despite the advantages to using a stepped wedge design for the PMP trial, we anticipate a number of challenges. The staggered entry into the intervention period means that clinics assigned to a later start date will start the intervention 48 weeks after their initial agreement to adopt the program. This may mean that the motivations for initially agreeing to adopt the program may no longer apply. We also anticipate that clinics may be frustrated by having to wait to start the program even if they stay motivated to participate. With that in mind, we defined a strategy to maintain clinic interest and engagement while they are waiting to start PMP. Each clinic will participate in a stakeholder committee where they will review implementation plans, handbooks, and undergo intervention training. The schedule for the stakeholder committee is staggered such that the later groups spend more time working in this venue in order to keep them engaged. A further potential problem in stepped wedge designs is contamination between clinics and those waiting for the intervention. It is possible that some clinics may change their procedures based on what they hear or see with other participating clinics. However, we expect such effects to be mild because meaningful and sustained improvements in mammography appointment adherence require systematic and prolonged effort that is unlikely to occur before the PMP training is completed.

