## Methods

### Trial design

We will conduct a non-randomized stepped wedge design as shown in Fig. 1. Each clinic will serve as its own control and will not have access to the PMP prior to implementation. Clinics will implement the PMP for up to 47 weeks depending on their group assignment (see Fig. 1). The trial will follow the CONSORT extension for stepped wedge randomized trials reporting guidelines (see Additional file 1). Insert reference: [Hemming K, Girling A, Haines T, et al. Protocol: Consort extension to stepped wedge cluster randomised controlled trial. 2014].

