### Intervention components

The PMP intervention program consists of the following components: a financial incentive of $7500 to the clinic for participation; funding for screening mammograms for women with documented financial need; coordination of increased screening within each clinic (the research team has established partnerships with local mobile mammography providers to assist in increasing screening capacity); 8 h of state certified training for staff in the EBI’s reminder phone call protocol [20, 30, 31]; stakeholder review of program adaptation and implementation materials; stakeholder meetings to troubleshoot implementation issues as they arise and to develop and disseminate e-newsletters and reports which highlight success stories and re-inforce desired behaviors; technical support for implementation (implementation manuals, clinic manuals, stakeholder manuals); and assistance in data tracking and reporting and budget impact analysis.

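### The waiting period used as comparator is said to be free of the PMP, yet the plan places intervention training and committee work in it; the sections must be reconciled and the training-to-launch window handled

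*Protocol article*

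**What the plan says.** **Control condition (Trial design).** "Each clinic will serve as its own control and will not have access to the PMP prior to implementation". Under Outcome measures, the primary comparison is the intervention period against the baseline period within each clinic, so the wait before launch is the comparator.

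**What the PMP consists of (Intervention components).** The list includes "8 h of state certified training for staff in the EBI’s reminder phone call protocol" and "stakeholder review of program adaptation and implementation materials; stakeholder meetings to troubleshoot implementation issues as they arise", together with implementation, clinic and stakeholder manuals.

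**What happens during the wait (Anticipated challenges).** Later clinics start 48 weeks after agreeing to take part. To hold their interest before the PMP starts: "Each clinic will participate in a stakeholder committee where they will review implementation plans, handbooks, and undergo intervention training". The schedule is staggered so that "the later groups spend more time working in this venue in order to keep them engaged".

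**Why contamination is expected to be mild (Anticipated challenges).** Sustained improvement is held to be "unlikely to occur before the PMP training is completed".

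**Where training is costed (Budget impact analysis).** The fixed cost of training navigators is assigned to the intervention period, not to the control period.

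**The concern.** Three sections cannot all be read literally. If the PMP includes staff training and stakeholder work, and clinics receive these while waiting, then clinics do have access to parts of the PMP before implementation. The Budget impact analysis adds a further inconsistency, because it books training to the intervention period.

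The consequence depends on behaviour. A navigator trained in the reminder-call protocol may begin to call or counsel patients differently before the official start. Appointments in that window would be analysed as control although partly treated, which pulls the estimated effect toward zero. Pre-start exposure grows with the length of the wait, so the distortion would follow start group, and the research team assigns start dates without randomization.

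The reassurance about contamination does not reach this case. It concerns clinics copying what they see elsewhere, and it relies on training not yet being complete. A clinic trained while waiting has passed that point.

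**Working it through.** **1. Side-by-side reading.** Items listed as PMP components that also appear in the waiting strategy are staff training in the intervention, stakeholder committee review of plans, and handbooks or manuals. Items listed as components but not said to reach clinics or patients during the wait are the reminder calls themselves, funding for mammograms and added screening capacity. Any pre-start exposure is therefore partial. No sentence dates training relative to launch, and none says how appointments after training but before launch are classified. Time to intervention start is named only as a possible control variable. Entered as a clinic-level covariate, it would not separate trained from untrained waiting time within a clinic.

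**2. The plan's own figure.** Inputs from Sample size: no-show 35% versus 28%, α 0.05 (taken as two-sided), power 0.9. With pooled variance under the null and mean rate 0.315:

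n = [1.960·√(2·0.315·0.685) + 1.2816·√(0.35·0.65 + 0.28·0.72)]² / 0.07² = (1.2876 + 0.8395)² / 0.0049 ≈ 923.3, rounded up to 924 per group. The stated figure reproduces.

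**3. Dilution throughout control time.** Let f be the share of the 7-point effect already present in control time. The documents give no f, so the range is an assumption. The control rate becomes 35% − 7f points and the contrast 7(1 − f) points.

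| f | Control rate | Contrast (points) | Power at 924 per group | n per group for 0.9 |
|---|---|---|---|---|
| 0 | 35.0% | 7.0 | 0.90 | 924 |
| 0.1 | 34.3% | 6.3 | 0.83 | 1134 |
| 0.2 | 33.6% | 5.6 | 0.74 | 1427 |
| 0.3 | 32.9% | 4.9 | 0.63 | 1852 |

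These powers belong to the uncorrected two-proportion comparison. They show the loss relative to the plan's own benchmark, not the power of the stepped wedge analysis.

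**4. Dilution in part of control time.** If only a share q of a clinic's control time follows training, its before-after contrast is 7(1 − q·f). With f = 0.3 and q = 1/3 this is 7 × 0.9 = 6.3 points instead of 4.9.

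**5. Gradient across groups.** Fig. 1 is not shown, so assume three groups of three clinics, four periods, one group starting at each step, and ICC 0.06. Let f be 0.1 for group 2 in period 2, and 0.2 then 0.3 for group 3 in periods 2 and 3.
- Group 1: 7.0 points.
- Group 2: 7(1 − 0.1/2) = 6.65 points.
- Group 3: 7(1 − 0.5/3) = 5.83 points.

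A generalized least squares model with period effects gives about 5.5 points. With a flat f of 0.2 in every waiting period after the first, the within-clinic contrasts are 7.0, 6.3 and 6.07, while the period-adjusted estimate is 7 × 0.8 = 5.6. The fall from period 1 to period 2 in waiting clinics is absorbed as calendar time, so a clean first period does not rescue that estimate. The relief in step 4 thus applies to the within-clinic contrast. Adjusting for period does not remove the dilution.

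**The case against.** The strongest reply is that the text does not show contamination. Training could come at the very end of the wait, so that almost no control appointments follow it. The Budget impact analysis supports this reading, since it places training cost in the intervention period, although that is cost accounting and not a timetable. The missing figure might also show a training phase. All of this stands. A reader might infer that trained clinics are certainly being counted as controls, but the article does not say so. It permits that outcome and does not exclude it.

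Second, the patient-facing element, the tailored call, is not said to be delivered before launch, and reviewing handbooks has no evident direct route to a patient's attendance. This also stands. A reader might suppose that preparation achieves a quarter or half of the full effect, but nothing in the documents supports any such share.

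Third, Trial status anticipates about 2200 women against 466 required, a ratio of 4.7. At f = 0.3 the requirement doubles (1852/924 = 2.0), or about 934 women on the plan's own arithmetic. Power may therefore be cushioned if that arithmetic is accepted. More women do not remove a bias in the estimate.

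Fourth, dilution is toward the null, so it does not undermine a positive finding. That is correct. It would make a small or null effect hard to interpret and understate the benefit.

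Fifth, analysis rules for such windows are commonly left to an SAP, which is not shown. Their absence is not an error here; the conflict between sections is.

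**Conclusion.** The point holds as a conflict in the text with a conditional consequence. Trial design, Intervention components, Anticipated challenges and Budget impact analysis do not agree on whether training and stakeholder work come before launch, and Outcome measures uses the pre-launch time as comparator. The reasoning that contamination will be mild does not cover clinics trained while waiting.

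Bias toward the null, largest in the late groups, follows only if training alters staff practice before launch. Its size cannot be derived from the documents. Under an assumed 10% to 30% carry-over throughout control time, the 7-point contrast becomes 6.3 to 4.9 points and benchmark power falls from 0.90 to 0.83 to 0.63. The within-clinic contrast is diluted less if only part of control time follows training. The graded example (about 5.5 points after period adjustment) rests in addition on an assumed layout.

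This should be corrected, but it does not invalidate the design.

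**What to change.** 1. Reconcile the four sections: state which PMP components are withheld until launch, which are delivered earlier, and when training falls relative to each clinic's start date.
2. Schedule the 8-hour reminder-call training immediately before each clinic's start. Committee engagement may continue during the wait.
3. Record the training completion date for each clinic.
4. Pre-specify a sensitivity analysis that excludes appointments between completion of call training and launch, or codes them as a transition state. Keep earlier waiting time, including committee time, as control.
5. Rewrite the contamination rationale so that it covers preparation within a waiting clinic as well as spillover between clinics.

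Excluding everything from the first committee session is not advised. With a 48-week wait in the late groups, it could remove much of the concurrent control data that separate the intervention from calendar time. The price of keeping committee time as control is that any effect of committee work alone remains in the comparator.

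Cost: some rescheduling, one date field per clinic, revised wording, and loss of a short window in one sensitivity analysis. Trial status reports that clinics are still collecting baseline measures, so the change looks feasible. Where training has already taken place, the recorded date and the sensitivity analysis still show whether the result depends on that window.

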### Ethical approval

This study has received approval from the Institutional Review Board at the University of Texas Health Science Center Houston. The protocol number is HSC-SPH-14-0269. Verbal consent will be obtained for patients participating in the EBI reminder phone calls. Written consent will be obtained for economic data collection from patients.
